##### Data-analysis and presentation/synthesis

At baseline, data from all planned and unplanned contact will be collected according to the scheme in Table 4. The instruments include variables of:

- *patient characteristics*: age, sex, socioeconomic status, smoking status and smoking history

- *medical outcomes*: FEV_1_, FeNO, ACQ, current treatment step, asthma medication

- *patient preferences*: FACCT, IPQ, BMQ, MARS

- *quality of life*: AQLQ, SF-36

- *patient utilities*: ASUI, SF-6D and EQ-5D, QALYs, e-TTO, number of limited activity days

- *costs*: health care consumption; CostQ

#### Economic evaluation

##### General considerations

The economic evaluation will compare differences in societal effects and costs to differences in the number of limited activity days (cost-effectiveness analysis, CEA) and quality adjusted life years (cost-utility analysis, CUA). The analysis will have a 12-months time horizon, without discounting. Group averages will be statistically compared using two-sided bootstrapping and net-benefit analysis will be used to relate costs to patient outcome. Sensitivity analyses will be performed on the perspective (societal versus health care) and the applied utility measure (Dutch EQ5D, SF6D, e-TTO, AQLQ-5D).

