**Design:**

720 Patients with mild to moderate persistent asthma from general practices with a practice nurse, age 18-50 yr, daily treatment with inhaled corticosteroids (more then 3 months usage of inhaled corticosteroids in the previous year), will be identified via patient registries of general practices in the Leiden, Nijmegen, and Amsterdam areas in The Netherlands. The design is a 12-month cluster-randomised parallel trial with 40 general practices in each of the three arms. The patients will visit the general practice at baseline, 3, 6, 9, and 12 months. At each planned and unplanned visit to the general practice treatment will be adjusted with support of an internet-based asthma monitoring system supervised by a central coordinating specialist nurse. Patient preferences and utilities will be assessed by questionnaire and interview. Data on asthma control, treatment step, adherence to treatment, utilities and costs will be obtained every 3 months and at each unplanned visit. Differences in societal costs (medication, other (health) care and productivity) will be compared to differences in the number of limited activity days and in quality adjusted life years (Dutch EQ5D, SF6D, e-TTO, VAS). This is the first study to assess patient preferences and cost-effectiveness of asthma treatment strategies driven by different target levels of asthma control.

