#### Patients

720 Patients with mild to moderate persistent asthma (prevalent cases) will be recruited from general practices via patient registries in three regions in The Netherlands:

- Leiden University Medical Center (LUMC) general practice network LEON (240 patients, 40 general practices)

- Radboud University Nijmegen Medical Centre general practice network (240 patients, 40 general practices)

- Amsterdam Medical Center (AMC) general practice network (240 patients, 40 general practices)

Only general practices with a practice nurse (or nurse practitioner/or physician assistant, further referred to as 'practice nurse') will participate (70% of general practices in the Netherlands currently have a employed such a professional [22]). Based on previous research experience in patients with asthma in general practice (SMASHING-project CME number P05.136), we estimate a response rate of 40% with an inclusion of 6 patients per 'standard' practice (i.e. practice with 2,300 patients) and 40 'standard' general practices per treatment strategy.

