##### Sample-size calculation

A minimally important change in patient utility (EQ-5D) has been defined as 0.074 point [42]. With 150 patients per treatment strategy we are able to detect at least a change of 0.06 points by net health benefit analysis [43] between the arms with a SD = 0.175 EQ-5D points (baseline data SMASHING-project; trial registry number NTR826: SD = 0.17) and a SD of €1000 for costs (SD = €816, usual care strategy [44]) and an increase in costs of €250 when a treatment strategy is not only more effective but also more costly, for a willingness-to-pay (WTP) of €30K (alpha = 0.05, one sided [43], beta = 0.20, one sided, rho costs-effects = 0) (Figure 2). With 40 clusters (general practices) per arm and assuming an intra-cluster correlation of 0.01, 0.07 and 0.11 the number of patients per cluster is 4, 5, and 6, and the total number of patients is 480, 600 and 720, respectively [45].

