##### Cost-effectiveness

The primary end-point is the evaluation of the cost-effectiveness of treatment strategies by incremental net-benefit analysis [43]. Net health benefit addresses cost-effectiveness ratios by assuming values for the willingness-to-pay per unit of effectiveness.

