##### Analysis of effectiveness

The differences in levels and changes in utilities based on EQ-5D, SF-6D, VAS, e-TTO and the number of limited activity days will be compared between the treatment strategies using a random-effects analysis accounting for within-patient repeated measurements and clustering on general practice.

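### The bootstrap stated for the primary net-benefit comparison is not tied to the general practice, the unit that is randomised

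*Protocol article*

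**What the plan says.** All references are to the protocol article.

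- **Unit of randomisation** (Abstract, Design): "The design is a 12-month cluster-randomised parallel trial with 40 general practices in each of the three arms".
- **Sample size** (Sample-size calculation): the calculation is for net health benefit and is then inflated for clustering, "assuming an intra-cluster correlation of 0.01, 0.07 and 0.11 the number of patients per cluster is 4, 5, and 6", so that "the total number of patients is 480, 600 and 720, respectively". The Patients section adopts the last case, with "an inclusion of 6 patients per 'standard' practice (i.e. practice with 2,300 patients) and 40 'standard' general practices per treatment strategy".
- **Primary end-point** (Economic evaluation, Cost-effectiveness): "The primary end-point is the evaluation of the cost-effectiveness of treatment strategies by incremental net-benefit analysis".
- **Inference for the economic comparison** (Economic evaluation, General considerations): "Group averages will be statistically compared using two-sided bootstrapping and net-benefit analysis will be used to relate costs to patient outcome". Neither this section nor the Cost-effectiveness and Cost analysis sections mention the practice or name the resampling unit.
- **Effectiveness** (Analysis of effectiveness): utilities and limited activity days are compared by a "random-effects analysis accounting for within-patient repeated measurements and clustering on general practice". Costs and net benefit are not among the outcomes listed there.

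**The concern.** The article describes how clustering is handled in two places, the sample size and the effectiveness model. It does not do so for the comparison that answers the trial's main question. There it names a bootstrap of group averages, which in its ordinary form draws patients independently within arm.

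The effectiveness model cannot fill the gap. A random-effects model of utilities gives no standard error for costs, for the covariance of costs and effects, or for net benefit.

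If patients from one practice resemble each other and the bootstrap draws them independently, standard errors for incremental costs, QALYs and net benefit are too small. A strategy could then be called cost-effective more often than the nominal error rate allows, although enough patients were recruited to pay for the clustering.

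**Working it through.** **1. The plan's own sample size.** Inputs from Sample-size calculation: difference 0.06 EQ-5D, SD 0.175, extra cost €250, cost SD €1000, willingness to pay €30,000, one-sided alpha 0.05, power 0.80, cost-effect correlation 0.

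- Net health benefit difference = 0.06 − 250/30,000 = 0.0517
- Variance = 0.175² + (1000/30,000)² = 0.03063 + 0.00111 = 0.03174, so SD = 0.1781
- n per arm = 2 × (1.645 + 0.842)² × 0.03174 / 0.0517², which gives 148 after rounding up, against 150 stated. A two-sided test would need 187, so the plan is one-sided here.

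**2. The plan's clustering allowance.** Design effect DE = 1 + (m − 1) × ICC, where m is the number of patients per practice. With 40 practices per arm, the m needed is 150 × (1 − ICC) / (40 − 150 × ICC).

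| ICC | m needed | m used | DE | 150 × DE | Per arm (40m) | Total |
|---|---|---|---|---|---|---|
| 0.01 | 3.86 | 4 | 1.03 | 154.5 | 160 | 480 |
| 0.07 | 4.73 | 5 | 1.28 | 192 | 200 | 600 |
| 0.11 | 5.68 | 6 | 1.55 | 232.5 | 240 | 720 |

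The stated totals are reproduced. N = 720 is the ICC 0.11 case.

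**3. Error rate if patients are resampled as independent.** The naive standard error is too small by a factor of √DE. Two-sided error = 2 × [1 − Φ(1.96/√DE)]; one-sided error = 1 − Φ(1.645/√DE); the interval is too narrow by 1 − 1/√DE.

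| ICC, m | √DE | Interval too narrow by | Two-sided 5% becomes | 95% interval covers | One-sided 5% becomes |
|---|---|---|---|---|---|
| 0.01, 4 | 1.015 | 1.5% | 5.3% | 94.7% | 5.3% |
| 0.07, 5 | 1.131 | 11.6% | 8.3% | 91.7% | 7.3% |
| 0.11, 6 | 1.245 | 19.7% | 11.5% | 88.5% | 9.3% |

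With the planned 6 patients per practice throughout, the two-sided errors are 5.6%, 9.2% and 11.5%. For the error to reach 10%, DE must be (1.960/1.645)² = 1.42, which at m = 6 means an ICC of (1.42 − 1)/5 = 0.084.

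**4. Simulation check.** Two arms of 40 practices, normal data, no true difference, percentile bootstrap with 500 draws, 2000 trials per scenario:

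| ICC, m | Patients resampled | Practices resampled |
|---|---|---|
| 0.01, 4 | 5.9% | 6.5% |
| 0.07, 5 | 8.7% | 5.7% |
| 0.11, 6 | 13.0% | 6.8% |

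Monte Carlo error is about 0.5 percentage points near 5% (√(0.05 × 0.95/2000) = 0.0049) and 0.7 near 11.5% (√(0.115 × 0.885/2000) = 0.0071). A second run of the last scenario with 300 draws gave 11.1% for patients and 5.9% for practices. The two patient-level results lie on either side of the formula's 11.5%.

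**5. Do the planning ICCs apply to net benefit?** The article gives no ICC specifically for net benefit. Under its own planning SDs and zero correlation, the utility term makes up 0.03063/0.03174 = 96.5% of the variance. At €30,000 the ICC of net benefit would therefore lie close to that of EQ-5D. Which outcome the planning ICCs describe is not stated.

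**The case against.** A reader might infer that the plan ignores practice clustering in its primary analysis, and so has about twice the nominal false-positive rate. The document does not support that, for these reasons.

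- **The resampling unit is not named.** A bootstrap that draws whole practices also compares group averages and fits the sentence. Nothing says that patients are treated as independent.
- **Doubling is conditional.** It needs patient-level resampling and an ICC of about 0.084 or more at 6 patients per practice. At ICC 0.01 the inflation is trivial.
- **The sentence has two clauses.** It does not expressly say that net benefit itself is tested by bootstrap, and the net-benefit method is referred to a cited source that is not at hand.
- **Bootstrap detail is often left to an analysis plan.** None is shown here, and it may name the unit.
- **The sample size for net benefit already carries a design effect.** This suggests that the authors had clustering in mind for this comparison.
- **The point should not be extended to acceptability curves.** The article mentions none.

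All of this limits the certainty of the point but does not remove it. The article itself states how clustering is treated for the effectiveness outcomes and names a method for the economic comparison without that link. If the bootstrap clause is not meant for net benefit, the primary end-point has no stated analysis that respects the practice at all. That the sample size anticipates clustering is a reason for the analysis to match it.

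**Conclusion.** The point holds in conditional form. The only inferential method stated for the economic comparison behind the primary end-point is not tied to the unit of randomisation, while the sample size and the effectiveness model both are, and the latter does not extend to costs or net benefit.

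The consequence ranges from negligible to serious over the plan's own scenarios: a true two-sided error between about 5.3% and 11.5% at a nominal 5%. The upper figure belongs to the scenario that sets the trial's size. This range rests on three assumptions that the document neither confirms nor excludes: patients are resampled independently, the planning ICCs apply to net benefit, and practices contribute equal numbers.

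**What to change.** Amend General considerations under Economic evaluation to state one of the following:

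1. General practices are resampled within arm (a cluster or two-stage bootstrap), keeping each patient's cost and QALY together as a pair.
2. Patient-level net benefit, or costs and QALYs jointly, is analysed in a mixed model with a random practice effect.

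Use the same method for incremental costs, incremental QALYs and incremental net benefit, so that the economic results agree with the effectiveness model.

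**Cost.** A sentence in the plan and a small change in the code; no new patients or data. If practice-level resampling was always intended, only the wording changes. Two limits should be recorded:

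- A simple practice-level bootstrap removes most of the excess but stays slightly liberal with 40 practices per arm, at about 6% to 7% in the simulation.
- Intervals become wider. The sample size already allows for this, but for a one-sided 5% test: with 240 per arm and DE 1.55, power is about 82% one-sided and 72% two-sided. The mismatch between one-sided planning and a two-sided bootstrap is a separate matter, but it should be settled in the same amendment.

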##### Cost-effectiveness

The primary end-point is the evaluation of the cost-effectiveness of treatment strategies by incremental net-benefit analysis [43]. Net health benefit addresses cost-effectiveness ratios by assuming values for the willingness-to-pay per unit of effectiveness.

##### Cost analysis

The cost analysis will include both medical (medication, visits, and hospitalizations) and non-medical costs (productivity losses, informal care). Purchased medication will be assessed from electronic patient records (with written patient permission), complemented with the patient's report on medication purchased elsewhere [46]. Other costs will be estimated using quarterly cost questionnaires (CostQ) [30]. Costs will be valued according to standard prices charges [47] including time and travel costs.

##### Analysis of effectiveness

The differences in levels and changes in utilities based on EQ-5D, SF-6D, VAS, e-TTO and the number of limited activity days will be compared between the treatment strategies using a random-effects analysis accounting for within-patient repeated measurements and clustering on general practice.

##### Patient outcome analysis

Utilities will be assessed every three months. In the base case analysis, quality-adjusted life years (QALYs) will be estimated using societal utilities obtained using the Dutch EQ5D tariff [48]. As sensitivity analyses, QALYs will be estimated using the SF-6D and individual utilities obtained using the e-TTO and visual analogue scale (transformed using a power transformation).

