**Figure 1 F1:**
[figure not shown]
**Flowchart of the ACCURATE trial**.

1 SUFF-strategy: achieving sufficiently controlled asthma based on conventional asthma control measures

2 STRICT-strategy: achieving strictly controlled asthma based on conventional asthma control measures

3 FeNO-strategy: achieving strictly controlled asthma based on conventional asthma control measures and an indirect marker of airways inflammation (FeNO).

General practices will be randomly assigned to the 3 groups using a computer generated permuted block scheme, ensuring concealment of allocation. Treatment assignment will be stratified according to characteristics of general practices (solo/duo/etc practice, rural/urban). The patients will visit the general practice for an introduction visit and control visits at baseline, 3, 6, 9, and 12 months. In case of asthma exacerbations patients pay an additional visit to the general practice or chest physician.

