#### Methods of measurements

At baseline, patient characteristics will be assessed including questions on atopy, smoking and symptom free days. In line with the Dutch national guidelines for general practitioners [3], patients are invited to visit their general practice every 3 months in order to titrate medication to the lowest level that is needed to achieve or maintain control. 3-Monthly care by the nurse practitioner will be organized similar to the advise in the national guidelines for general practitioners [5], including questions on asthma control, medication, adverse events and measurement of lung function. At all planned and unplanned visits questionnaires will be performed at home (Table 4). In addition, the ACQ will be performed at home monthly as an outcome measure. Peripheral blood will be obtained at baseline. Both paper and electronic versions will be used to collect the data, depending on the preference of a patient. Electronic versions in the ACCURATE project will be similar to those from the SMASHING project http://www.netquestionnaires.nl. A coordinating nurse specialist will supervise the nurse practitioners.

**Table 4 T4:** Instrument Table

	Assessment of level of asthma control:			Outcomes									
	driving treatment step												
				Patient preferences			Quality of life			Patient utilities			Costs
	airway inflammation	lung function	asthma control	beliefs about medicines	adherence	adherence	patient statisfaction	generic	asthma related	patient perspective	asthma related	societal perspective	health care + other costs
	FeNO	FEV_1_	ACQ	IPQ	MARS	BMQ	FACCT	SF-36	AQLQ	TTO	ASUI	EQ-5D	CostQ
**Baseline**	X	X	X	X	X	X	X	X	X	X	X	X	X
**Unplanned visit**	F	X	X						X		X	X	
**3 months**	F	X	X						X		X	X	X
**6 months**	F	X	X	X	X	X	X	X	X	X	X	X	X
**9 months**	F	X	X						X		X	X	X
**12 months**	X	X	X	X	X	X	X	X	X	X	X	X	X

X in all treatment strategies, F only in FeNO strategy

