##### Quality of life, patient utilities

- quality of life: Asthma Quality of Life Questionnaire (AQLQ) [36] and Short-Form 36 (SF-36) [37]

- patient utilities: the Asthma Symptom Utility Index (ASUI) [38]. Patient utilities will additionally be assessed by the time-trade-off method by telephonic interview and a web-page (e-TTO) at each planned and unplanned period (exacerbation) [39]

- indirect utilities from the general public will be obtained using the SF-6D [37,34] and EQ-5D [40,41]. This allows the calculation of quality adjusted life years (QALYs).

- number of limited activity days by questionnaire

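### The text and Table 4 give different measurement schedules for e-TTO, and by implication for SF-6D, so the sensitivity QALYs may rest on three time points against five for the EQ-5D base case

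*Protocol article*

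**What the plan says.** All references are to the protocol article.

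- **Patient outcome analysis.** "Utilities will be assessed every three months". The base-case QALY uses the Dutch EQ-5D tariff. The section then adds: "As sensitivity analyses, QALYs will be estimated using the SF-6D and individual utilities obtained using the e-TTO and visual analogue scale".
- **Quality of life, patient utilities.** Patient utilities are also obtained by the "time-trade-off method by telephonic interview and a web-page (e-TTO) at each planned and unplanned period (exacerbation". For the other measures it says "indirect utilities from the general public will be obtained using the SF-6D" and the EQ-5D, without giving a frequency.
- **Design (text under Figure 1).** There are "control visits at baseline, 3, 6, 9, and 12 months".
- **Abstract, Design.** Utilities, among other data, are collected three-monthly and at unplanned visits. SF6D and e-TTO are listed among the QALY measures.
- **Table 4 (Methods of measurements).** SF-36 and TTO are marked at baseline, 6 and 12 months. Both are blank at 3 months, at 9 months and at unplanned visits. EQ-5D, ASUI and AQLQ are marked in every row. The legend, "X in all treatment strategies, F only in FeNO strategy", gives no exception that would fill the blanks.
- **Data-analysis and presentation/synthesis.** Data from planned and unplanned contacts follow the Table 4 scheme.

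**The concern.** The article gives two collection schedules for the same instrument. For e-TTO they cannot both be carried out: the text calls for five planned measurements plus one at each exacerbation, while the table calls for three and none at exacerbations. A study team working from the table would not collect what the text promises, and no later analysis plan can recover utilities that were never collected.

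What is at stake is how the sensitivity analysis reads. Under Economic evaluation, the utility measure is varied to see whether the cost-effectiveness conclusion depends on it. If EQ-5D is integrated over five points and SF-6D and e-TTO over three, a difference between base case and sensitivity analysis may come from the instrument or from the measurement grid. Treatment can be adjusted at every three-monthly visit, so a difference between arms that appears or changes within the first six months is plausible. The level-and-change comparisons of SF-6D and e-TTO under Analysis of effectiveness would likewise have fewer time points than the text suggests.

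**Working it through.** **Step 1. Count the schedule.** Three-monthly assessment over 12 months means 0, 3, 6, 9 and 12 months, which is five planned points. Table 4 has 13 instrument columns, and each visit row resolves to 13 cells, so the blanks are not a column shift. They also form a coherent pattern: IPQ, MARS, BMQ, FACCT, SF-36 and TTO all drop out together at 3 and 9 months.

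| Utility source | Text | Table 4, planned | Table 4, unplanned |
|---|---|---|---|
| EQ-5D | three-monthly (general statement) | 0, 3, 6, 9, 12 | yes |
| ASUI | three-monthly (general statement) | 0, 3, 6, 9, 12 | yes |
| SF-36, for SF-6D | three-monthly (general statement only) | 0, 6, 12 | no |
| TTO | every planned and unplanned period (specific statement) | 0, 6, 12 | no |

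The five-point schedule is reproduced for EQ-5D and ASUI. It is not reproduced for SF-36 or TTO.

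**Step 2. Weights.** The article names no QALY interpolation rule, so the trapezoid is assumed here. With time in years, each interval of length h gives h/2 to each of its ends.

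- Five points (h = 0.25): 0.125, 0.25, 0.25, 0.25, 0.125.
- Three points (h = 0.5): 0.25, 0.50, 0.25.

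On the five-point grid, months 3 and 9 together carry 0.25 + 0.25 = 0.50 of the weight. Under Table 4 neither SF-6D nor e-TTO is observed at those months.

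**Step 3. Illustrative effects.** The between-arm gain is set at 0.06, the detectable EQ-5D difference in the sample-size section. The time profiles are assumptions, because the article gives none.

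| Gain at 0, 3, 6, 9, 12 months | Five points | Three points |
|---|---|---|
| 0, 0.06, 0.06, 0.06, 0.06 | 0.06 × 0.875 = 0.0525 | 0.06 × 0.75 = 0.045 |
| 0, 0.03, 0.06, 0.06, 0.06 | 0.03 × 0.25 + 0.06 × 0.625 = 0.045 | 0.045 |
| 0, 0, 0.06, 0.06, 0.06 | 0.06 × 0.625 = 0.0375 | 0.045 |
| 0, 0.06, 0, 0, 0 | 0.06 × 0.25 = 0.015 | 0 |

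In the first profile the coarser grid loses 0.0075 QALY, or 0.0075/0.0525 = 14%. In the second it loses nothing. In the third it overstates the gain by 0.0075. The fourth is an extreme case, in which the whole effect falls between two observed points. The discrepancy can therefore have either sign, or be zero, depending on the true time course.

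**The case against.** The strongest reply has four parts.

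1. **SF-6D.** No sentence gives SF-6D its own frequency. The general statement on utilities could refer to EQ-5D, the base-case measure named next, and ASUI, both of which are three-monthly in Table 4. The abstract is loose in other respects: it also puts adherence and costs at three-monthly and unplanned visits, whereas Table 4 has MARS only at 0, 6 and 12 months and no CostQ at unplanned visits. This stands. The SF-6D conflict is one of implication; only the e-TTO conflict is explicit.
2. **Feasibility.** A reader might infer that the SF-6D and e-TTO QALYs cannot be built. The documents do not support that. QALYs can be formed from 0, 6 and 12 months, and the article never says that the sensitivity QALYs use five points.
3. **Interpretability.** A reader might also infer that a disagreement with the base case could never be interpreted. That goes too far as well. EQ-5D is collected at 0, 6 and 12 months in all arms, so a matched comparator can be computed from data already planned.
4. **Size.** The magnitudes depend on an assumed integration rule and on chosen profiles, and one reasonable profile gives no difference. This stands, and it is why the figures are given only as an illustration.

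The contradiction itself remains. The interpolation rule and additional sensitivity runs may properly be left to an analysis plan that is not shown. Two incompatible collection schedules for e-TTO in the current text are a different matter, since they determine which data will exist.

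**Conclusion.** The text and Table 4 disagree on when e-TTO is measured, and, if the statement on utilities covers every utility instrument, on SF-6D too. Under Table 4 the sensitivity QALYs from these two measures use three time points against five for EQ-5D, and none of the exacerbation e-TTO values promised in the text would be collected. A change of instrument is then mixed with a change of measurement times. With a 0.06 gain, a trapezoid and the assumed sustained profiles, the grid alone shifts the QALY difference by between −0.0075 and +0.0075, including zero; a purely transient gain at month 3 would be missed altogether (0.015 against 0).

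The reach is limited. The base-case EQ-5D QALY, the primary incremental net-benefit analysis built on it and the sample size, which uses EQ-5D inputs, are unaffected. The point concerns the SF-6D and e-TTO sensitivity QALYs and the amount of data behind the repeated-measures comparisons of those two measures.

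**What to change.** Reconcile Table 4 with the abstract's Design paragraph, the section on quality of life and patient utilities, and the section on patient outcome analysis. There are two ways to do so:

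- **If the 0, 6 and 12 month schedule is intended:** state it explicitly for SF-6D and e-TTO, correct the sentence that places e-TTO at every planned and unplanned period, and add an EQ-5D QALY recalculated from 0, 6 and 12 months. Comparing that with the SF-6D and e-TTO QALYs isolates the instrument; comparing it with the five-point EQ-5D QALY isolates the grid. The cost is a text correction and one extra calculation, with no burden on patients.
- **If three-monthly measurement is intended:** mark SF-36 and TTO at 3 and 9 months in Table 4, and mark TTO at unplanned visits if the exacerbation values are wanted. This costs two further rounds of both instruments per patient, plus the unplanned e-TTO assessments.

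### The primary net-benefit comparison names no baseline EQ-5D, baseline cost or stratum term, which gives up precision that data already collected could supply

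*Protocol article*

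**What the plan says.** Under Cost-effectiveness: "The primary end-point is the evaluation of the cost-effectiveness of treatment strategies by incremental net-benefit analysis". How the arms are compared is stated under Economic evaluation, General considerations: "Group averages will be statistically compared using two-sided bootstrapping and net-benefit analysis will be used to relate costs to patient outcome". The sensitivity analyses listed there vary the perspective and the utility measure; none varies the adjustment. The Patient outcome analysis section adds only the tariff: "In the base case analysis, quality-adjusted life years (QALYs) will be estimated using societal utilities obtained using the Dutch EQ5D tariff".

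A separate model appears under Analysis of effectiveness. It compares "The differences in levels and changes in utilities based on EQ-5D, SF-6D, VAS, e-TTO and the number of limited activity days" between strategies, "using a random-effects analysis accounting for within-patient repeated measurements and clustering on general practice". It covers utilities and limited activity days. It does not cover QALYs, costs or net benefit, and it names no strata.

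The data for adjustment exist. Table 4 marks EQ-5D and CostQ at baseline for all strategies, and the Design section stratifies the allocation of practices by practice type and by rural or urban location.

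**The concern.** Utilities are measured at baseline and every three months. If the 12-month QALY is the usual area under the utility curve (an assumption, since the article does not give the construction), it begins at the baseline value. A chance difference in baseline EQ-5D then passes into the QALY difference, both directly and through the correlation between visits. Because practices are randomised, such differences are larger than under individual randomisation with the same number of patients.

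A comparison of group averages leaves this variation in the error of the primary result. A regression on baseline removes much of it. What is at stake is the width of the interval for incremental net benefit, and hence the chance of a clear answer.

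The utility model raises a smaller, related matter. Levels and changes are two comparisons that treat baseline differently: a comparison of levels makes no use of it, and a simple change score over-corrects whenever the correlation is below 1. They can therefore give different answers from the same data.

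**Working it through.** **Inputs from Sample-size calculation:** effect 0.06 EQ-5D points; SD 0.175; cost increase €250; cost SD €1000; willingness to pay €30,000; one-sided alpha 0.05; power 0.80; cost-effect correlation 0; 150 per arm before clustering; 40 practices per arm; 4, 5 or 6 patients per practice for ICC 0.01, 0.07 or 0.11.

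**1. The plan's own figures.**
- Net-benefit effect in QALY units: 0.06 − 250/30000 = 0.0517.
- SD: √(0.175² + (1000/30000)²) = √(0.030625 + 0.001111) = 0.1781.
- n per arm: 2(1.645 + 0.842)² × 0.1781²/0.0517² ≈ 147.0, rounded up to 148. The stated 150 is reproduced (power 0.807 at 150).
- Clustering: 150 × [1 + (m − 1) × ICC]/40 = 3.86, 4.80 and 5.81, so m = 4, 5, 6 and totals of 480, 600 and 720, as stated.

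The calculation uses the full SD of 0.175, so it takes no credit for baseline adjustment.

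**2. Size of chance imbalance, at 240 per arm (6 per practice).**
- ICC 0.11: effective n = 240/1.55 = 154.8; SE = 0.175 × √(2/154.8) = 0.0199.
- ICC 0.01: effective n = 240/1.05 = 228.6; SE = 0.175 × √(2/228.6) = 0.0164.

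**3. Carry-over into the QALY difference.** Let r be the correlation between baseline EQ-5D and the 12-month QALY. The article gives no value, so 0.3, 0.5 and 0.7 are assumed. With equal SDs, a one-SE imbalance at ICC 0.11 moves the unadjusted QALY difference by r × 0.0199 = 0.006, 0.010 or 0.014. That is 12%, 19% or 27% of the net-benefit effect of 0.0517.

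**4. Power with adjustment.** The adjusted SD is √(0.175²(1 − r²) + (1000/30000)²). Two-sided power at 0.05 is Φ(0.0517/SE − 1.96), with SE = SD × √(2/154.8).

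| r (assumed) | SD | n per arm before clustering, one-sided | One-sided power, 240 per arm, ICC 0.11 | Two-sided power, same |
|---|---|---|---|---|
| unadjusted | 0.178 | 148 | 0.818 | 0.723 |
| 0.3 | 0.170 | 135 | 0.847 | 0.761 |
| 0.5 | 0.155 | 112 | 0.901 | 0.834 |
| 0.7 | 0.129 | 78 | 0.969 | 0.940 |

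The two-sided column matches the two-sided bootstrap in the economic section. The step from 0.818 to 0.723 comes from sidedness, not from the lack of adjustment.

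**5. Sensitivity to how the QALY is built.** Step 4 gives the QALY the planning SD of 0.175. Suppose instead a trapezoid over five visits (weights 0.125, 0.25, 0.25, 0.25, 0.125) with equal between-visit correlation of 0.5 or 0.7, also assumed.
- Slope of QALY on baseline: 0.125 + 0.875 × 0.5 = 0.56, or 0.125 + 0.875 × 0.7 = 0.74.
- QALY variance as a share of 0.175²: the squared weights sum to 0.21875, so the share is 0.21875 + 0.78125 × 0.5 = 0.61, or 0.77 at 0.7.
- Share of QALY variance removed by adjustment: 0.5625²/0.609 = 52%, or 0.7375²/0.766 = 71%.

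Here the unadjusted comparison is already more precise than planned. At 0.5, the unadjusted SE is √(0.609 × 0.030625 + 0.001111) × √(2/154.8) = 0.0160 and two-sided power is Φ(0.0517/0.0160 − 1.96) ≈ 0.90. At 0.7 the same formula gives SE 0.0178 and power about 0.83. Adjustment still narrows the interval, but there is less power left to gain.

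No figure can be given for baseline costs or the strata, because the article states no correlation or SD for them.

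**The case against.** The strongest reply is that the article never calls the averages raw or unadjusted. A bootstrap of group averages could hold regression-adjusted averages, and covariate lists are often left to a full protocol or analysis plan, which is not shown here. That stands as far as it goes: a reader might infer that adjustment is ruled out, and the text does not say so. The point survives as an improvement to the one comparison the article does state, not as a complaint about missing detail.

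Second, randomisation makes chance imbalance part of sampling variance. An interval that respects clustering already covers it, and the planned size assumed no adjustment. This stands in full. A reader might infer that the result would be biased or the trial undersized on this account; neither follows.

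Third, a reader might infer that baseline is used nowhere. The effectiveness section contradicts this, since it compares changes in utilities. In a repeated-measures model, change could also be an arm-by-time effect, not a subtraction; the article does not say which.

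Fourth, it is tempting to set the shift against the €250 planning cost difference. The design net-benefit effect, 0.0517 × €30,000 ≈ €1,550, is the fairer yardstick, and the SE of 0.020 belongs to the largest of the three listed ICCs.

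Finally, nothing in the article shows that region affects EQ-5D or costs, so the absence of region from the strata is not a fault.

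**Conclusion.** The point holds as a recommended improvement in efficiency. The stated comparison for the primary endpoint uses no baseline or stratum information, although all of it is available. On the planning SD, at 240 per arm and ICC 0.11, two-sided power would rise from 0.72 to between 0.76 and 0.94.

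That range rests on an assumed correlation of 0.3 to 0.7 between baseline EQ-5D and the QALY, on the same ICC before and after adjustment, and on a QALY SD of 0.175. If the QALY SD is smaller, as a trapezoid would make it, power starts higher and the gain in power shrinks, although the interval still narrows. The documents do not support a finding of bias, of a sample-size error, or of a declared refusal to adjust.

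**What to change.** In Economic evaluation, General considerations, state that incremental QALYs, costs and net benefit are estimated by regression on arm. Include baseline EQ-5D for QALYs, baseline CostQ cost for costs, and practice type and rural/urban location for both, and run the regressions inside a bootstrap that resamples whole practices. Region may be added as an optional covariate.

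In Analysis of effectiveness, replace the separate comparisons of levels and of changes with one random-effects model of follow-up utilities, with baseline utility as a covariate and the existing patient and practice terms kept.

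Fix both before the outcome data are compared by arm. The cost is analysis wording only: every variable is already collected, and the sample size need not change.
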